### Phase 2: Exploring Stakeholders’ Perceptions of Health Literacy Status in Rural Communities Surrounding Protected Areas

#### Overview

Phase 2 will use focus group discussions (FGDs) and in-depth interviews to achieve objective 2, which is to obtain stakeholders' opinions on health literacy issues among the community in PNP. The results will support the findings for objective 1.

#### Sample Selection

The selection of the stakeholders will be based on 3 categories, namely, government entities, knowledge-generating institutions, and civil society organizations [19,20]. However, the number of these actors will vary. This method will use purposive sampling to obtain a precise sample size. The expected actors can nominate any other actors with potential contributions to PNP's health literacy issue. This process will be halted when the answers given by the respondents are saturated [21].

#### Data Coding and Analysis

Data extraction and coding will be done for all Net-Map exercises, with a focus on thematic analysis utilizing information from the interviews. This analysis will mainly involve mapping activities and explaining the impact of protected areas on health literacy. The thematic analysis will follow a 2-step coding process. First, a line-by-line review of the interview data will be conducted to identify the key impacts related to the study objectives. Subsequently, each article will be assigned a code label to cluster all the information into a common theme.

### Phase 3: Identifying Health Literacy and Its Associated Factors in Rural Communities Surrounding Protected Areas

#### Participants and Sampling

This study will focus on the PNP. It covers 2477 square kilometers and was the country’s first national park established in Malaysia between 1938 and 1939, originally known as the King George V National Park. Following Malaysia's independence from British rule in 1957, the park was renamed. It is comprised of 3 protected areas in the states of Pahang, Kelantan, and Terengganu to form the central spine of Peninsular Malaysia. The national park has a reputation for being one of the world's oldest tropical rainforests, with an estimated age of 130 million years and a size of 4343 square kilometers.

Local communities in PNP are composed of Malay and Orang Asli (Batek and Semak Beri ethnicities). This location meets the criteria for this study because a protected area has been established and legal and other institutional measures have been established to promote them. The Pahang Department of Wildlife and National Parks (PERHILITAN) manages the PNP. The area is not open to the public except for those who have received prior approval from the authority for research purposes and minimal tourism activity at Kuala Tahan. Currently, the wildlife reserve contains a single research center that serves 2 distinct goals. The national park was originally established at Ulu Tembeling, with the first superintendent's office situated at Kuala Tahan. The southern section of PNP features a river boundary of over 80 kilometers along Sungai Tembeling, the Hulu Tembeling basin's principal river. Indigenous people inhabit the national park, while the Malay community resides near the river. For this study, respondents were drawn from the Malay and indigenous communities from the provinces of Hulu Tembeling and Tembeling Tengah. Table 1 shows the total number of respondents.

Respondents aged 18 years and above may vary in health status, including those with disabilities. A stratified random sampling approach (based on villages) will be employed for both the Hulu Tembeling and Tembeling Tengah provinces. All villages will be identified and visited. The choice of houses in the village will be selected randomly based on the number of houses given by the head of the village (Tok Empat and Tok Batin) and the inclusion criteria among the respondents, such as being able to read, having no cognitive disabilities, and being willing to participate in the survey.

**Table 1 table1:** The total number of respondents and sample in Pahang National Park (PNP).

Name of village	Race	Province	Head of households (N=2525), n (%)	Sample (N=400), n (%)
Kg Pagi	Malay	Hulu Tembeling	95 (3.8)	15 (3.8)
Kg Kuala Sat	Malay	Hulu Tembeling	142 (5.6)	22 (5.6)
Kg Bantal	Malay	Hulu Tembeling	155 (6.1)	25 (6.1)
Kg Gusai	Malay	Hulu Tembeling	70 (2.8)	11 (2.8)
Kg Bukit Mat Daling	Malay	Hulu Tembeling	141 (5.6)	22 (5.6)
Kg Kuala Tahan	Malay	Tembeling Tengah	657 (26.0)	104 (26.0)
Kg Gol/Lik	Malay	Tembeling Tengah	40 (1.6)	6 (1.6)
Kg Merting/Lubok Payung	Malay	Tembeling Tengah	111 (4.4)	18 (4.4)
Kg Labu/Jong Berlabuh	Malay	Tembeling Tengah	163 (6.5)	26 (6.5)
Kg Pasir Sia/Air Hitam	Malay	Tembeling Tengah	86 (3.4)	14 (3.4)
Kg Selimbar/Chebong	Malay	Tembeling Tengah	58 (2.3)	9 (2.3)
Felda Sg Retang	Malay	Tembeling Tengah	509 (20.2)	81 (20.2)
Kuala Atok	Batek	Tembeling Tengah	35 (1.4)	6 (1.4)
Sungai Tiang	Semoq Beri	Tembeling Tengah	60 (2.4)	10 (2.4)
Sungai Tekal	Semoq Beri	Tembeling Tengah	83 (3.3)	13 (3.3)
Bukit Gam	Batek	Tembeling Tengah	22 (0.9)	3 (0.9)
Sg Keniam	Batek	Tembeling Tengah	35 (1.4)	6 (1.4)
Jeram Aur	Batek	Tembeling Tengah	13 (0.5)	2 (0.5)
Jeram Dedari	Batek	Tembeling Tengah	17 (0.7)	3 (0.7)
Sungai Yong	Batek	Tembeling Tengah	18 (0.7)	3 (0.7)
Sg Tabung/ Teresek	Batek	Tembeling Tengah	15 (0.6)	2 (0.6)

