#### Inclusion and Exclusion Criteria

Participants in this study are required to be adults aged 18 or above and will be recruited after providing consent. Age verification will be based on their ID cards. Potential respondents may either be healthy or have various physical disabilities and demonstrate a willingness to participate. Additionally, they must be able to communicate in the Malay language. However, people with cognitive impairments will be excluded from the study.

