#### Data Collection Procedure

A total of 8 interviewers will be required to conduct the survey, working in pairs. For security and dialect reasons, a local representative will be appointed to accompany each team. Before the data collection, the ground staff will introduce the interviewers to the household members to ensure that the head of the household and other members are present and grant permission for the interviewers to enter their personal premises. Once approval is obtained, the interviewer will explain the nature of the study based on the participants’ information sheet, which outlines the key details. Subsequently, the information sheet will be provided to the participants for their reference. In addition, the interviewers will reassure the participants that the information provided in the study will remain confidential and their participation is entirely voluntary. The face-to-face interview will begin shortly after the head of the household and other household members have signed the consent form. During the interview, the respondents’ height and weight will be measured, contingent on suitability and participant preference. If the head of the household is absent during the visit, the house will be marked on the map, and a second visit will be arranged for the next day. However, the house will be excluded if the head of the household is still not present during the second visit.

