### Ethical Considerations

Ethics approval for this study was granted by the Universiti Sains Islam Malaysia (USIM) Research Ethics Committee (USIM/JKEP/2022-216). Each respondent will sign a written informed consent form before the interview. Academic journals, conferences, and stakeholder seminars will be used to communicate the findings of this research. The protocol received approval from the International Standard Randomized Controlled Trial Number Registry (ISRCTN; 40626062).

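### The Phase 3 survey has two conflicting eligibility lists: one requires reading ability and the other does not. If the reading rule is applied, a health literacy survey selects on a trait plausibly tied to its own outcome.

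*Protocol article*

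**What the plan says.** Two sections of the Protocol article set eligibility for the same Phase 3 survey.

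- **Participants and Sampling.** Houses are chosen at random within villages, subject to inclusion criteria for respondents "such as being able to read, having no cognitive disabilities, and being willing to participate in the survey".
- **Inclusion and Exclusion Criteria.** "Participants in this study are required to be adults aged 18 or above and will be recruited after providing consent". Health status may vary and physical disability is no bar. "Additionally, they must be able to communicate in the Malay language". The one stated exclusion is: "However, people with cognitive impairments will be excluded from the study". Reading is not mentioned.

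On how the survey is run, Data Collection Procedure says that "the interviewer will explain the nature of the study based on the participants’ information sheet, which outlines the key details", that the sheet is then handed over, and that "The face-to-face interview will begin shortly after the head of the household and other household members have signed the consent form". A local representative accompanies each team, partly for dialect. Ethical Considerations adds: "Each respondent will sign a written informed consent form before the interview".

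The outcome is the HLS-SF-Q12 (Tools and Instruments, Table 4), in which respondents rate how hard they find health-related tasks. Objective 3 (end of the Introduction) concerns the health literacy status of rural communities near protected areas, with no restriction to people who can read. The Strengths and Limitations section does not mention an exclusion of non-readers.

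**The concern.** A field team that meets an adult who speaks Malay, consents and cannot read would turn that person away under one section and enrol them under the other. Eight interviewers work in pairs, so practice could differ between teams and villages.

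The trait in dispute is close to what the survey measures. The Introduction describes these communities as having little schooling and difficulty obtaining and understanding health information. Adults who cannot read plausibly sit toward the low end of the scale. Leaving them out would probably raise the estimated share with adequate health literacy. It would also narrow the spread of education, which is one of the sociodemographic factors whose association with health literacy is to be tested (Data Entry and Analysis). A larger sample would not remove an error of this kind. The survey results also inform the choice of intervention in Phase 4.

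**Working it through.** **Step 1: set the two lists side by side.**

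| Criterion | Participants and Sampling | Inclusion and Exclusion Criteria |
|---|---|---|
| Age 18 or above | yes | yes |
| Willing to take part | yes | yes |
| No cognitive impairment | yes | yes |
| Communicates in Malay | not stated | yes |
| Able to read | **yes** | **not stated** |

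The lists differ on two items. The reading item decides whether a group of adults belongs to the target population.

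**Step 2: does the procedure need reading?** The survey is a face-to-face interview and the study is explained orally. The article does not say in so many words that each item is read aloud. The written steps for the respondent are the information sheet, which is also explained orally, and the signed consent form. Neither is given as the reason for the reading criterion.

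**Step 3: illustrate the size if the reading rule is applied.** The plan states no figure to reproduce here.

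Let u be the share of adults who cannot read, p_r the proportion adequate among readers and p_n the proportion adequate among non-readers. The true proportion is (1 − u)·p_r + u·p_n. A readers-only survey estimates p_r. So:

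overstatement = u × (p_r − p_n)

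Inputs:
- p_r = 35.5%. This is the national prevalence in the Sample Size section, read here as the share with adequate health literacy and assumed to hold for readers in this area.
- p_n = 0%, 10% or 20%. Assumed.
- u = 10%, 20% or 30%. Assumed.

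| u | p_n = 0% | p_n = 10% | p_n = 20% |
|---|---|---|---|
| 10% | 0.10 × 35.5 = 3.55 | 0.10 × 25.5 = 2.55 | 0.10 × 15.5 = 1.55 |
| 20% | 7.10 | 5.10 | 3.10 |
| 30% | 10.65 | 7.65 | 4.65 |

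(percentage points; zero if readers and non-readers do not differ)

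**Step 4: compare with sampling error.** The 95% half-width at the planned n=400, under simple random sampling, is 1.96 × √(0.355 × 0.645 / 400) = 0.0469, or about 4.7 points.

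The overstatement reaches 4.69 points when u = 4.69/35.5 = 13.2% if no non-reader is adequate, or u = 4.69/15.5 = 30.3% if 20% of them are. Below those shares it is smaller than the sampling error.

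**The case against.** **The exclusion may never happen.** The section headed as the eligibility criteria has no reading rule, and the other list opens as a set of examples inside a sampling sentence. A reader might infer that the lowest-literacy adults are definitely cut out. The documents do not support that, because it follows only if the sampling section governs. This objection stands, and the bias must be stated conditionally. The contradiction remains either way.

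**The size is assumed.** This also stands. A reader might suppose a gap of 50 points between readers and non-readers, giving 0.30 × 50 = 15 points at 30% non-readers. If readers are near 35.5%, the gap cannot exceed 35.5 points, so the ceiling at that share is 10.65. At 10% non-readers the overstatement is below the sampling error. If the article's prevalence meant limited rather than adequate health literacy, the readers' figure would be 64.5% and the ceilings would rise. The article does not spell this out.

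**No margin is stated.** A reader might take ±5 points as the planned precision behind the prevalence-based size of 323. The Sample Size section gives no precision, so the comparison above uses the half-width computed at n=400.

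**The outcome does not test reading.** The HLS-SF-Q12 records perceived difficulty across access, understanding, appraisal and application. A link with reading ability is plausible but its strength is unknown, so it cannot be called a near-substitute for the outcome. It is likewise tempting to say that the bias is larger in the indigenous villages, which hold 48 of the 400 planned respondents in Table 1. No section gives reading ability by ethnicity, so that is conjecture.

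**Signed consent may explain the rule.** This is a fair possibility, though the article does not say so. A signature after an oral explanation does not by itself require reading, but any change has to deal with consent openly.

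**Conclusion.** The point holds as a contradiction with a conditional bias. The Protocol article gives two incompatible eligibility lists for one survey, and they differ on a trait plausibly related to the outcome. That part is certain from the text.

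If the reading rule is applied, the estimate describes readers, not the communities in objective 3, and probably overstates the share with adequate health literacy. On the assumed inputs the overstatement is 1.55 to 3.55 points at 10% non-readers and 4.65 to 10.65 points at 30%, against a half-width of about 4.7 points. It could therefore be minor or could exceed the sampling error. The documents do not settle which, because they give neither the share of non-readers nor their health literacy.

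**What to change.** 1. Delete the ability to read from Participants and Sampling, so that the criteria under Inclusion and Exclusion Criteria apply throughout.
2. State in Data Collection Procedure that the interviewer reads every item aloud, including the HLS-SF-Q12.
3. Ask the ethics committee to confirm a consent route for adults who cannot read, since the present procedure rests on a signed written form.
4. Record reading ability for each respondent, use it as a covariate, and give a readers-only result as a sensitivity analysis.
5. Enrolment is reported as ongoing (Results). Where respondents have already been screened under the reading rule, state that criterion in the eligibility section, report exclusions by village and ethnicity where they were recorded, and limit those conclusions to adults who can read. Do not pool the two screening regimes without saying so.

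The cost is a small consent amendment, one added survey item and somewhat longer interviews with non-readers. Interviewers and local representatives are already planned, so no extra staff should be needed.

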#### Sample Size

Two approaches will be considered to calculate the optimal sample size (ie, using the odds ratio [OR] and prevalence). The selection will be based on the method producing the higher sample size. For the OR, the sample size will be calculated using the OR of health literacy in Malaysia [22], identified as 3.41 with a 95% CI. We will use the Open Epi Software (version 3.01) to calculate the sample size. With an OR of 3.41, the estimated sample size is 310 as shown in Table 2. Furthermore, Table 3 shows the comparison of sample sizes for exposed and nonexposed groups in Kelsey and Fleiss methods.

In contrast, the second method uses prevalence. In Malaysia, the health literacy prevalence among individuals aged 18 years and above is 35.5% [23]. Using this percentage, the minimum sample size calculated for this study is 323 people for a 95% CI. Since the prevalence sample size is higher than the OR, we decided to use it as our sample size. Considering a dropout probability of approximately 10%, the total sample size needed for this study is about 355 people. However, we will distribute a sample size of 400 people based on the ratio calculated. We estimate that out of 400 adults, approximately 200 households will need to be interviewed based on the assumption that 1 household has 2 adults. To ensure that the provinces within the national park are well represented, the percentage of the selected population is determined to be 24%, 64%, and 12% for Malay in Hulu Tembeling, Tembeling Tengah, and indigenous people, respectively. Using the stratified random sampling techniques, the number of samples allocated for each village is outlined in Table 1.

**Table 2 table2:** The estimated sample size.

Variables	Values, n
Sample size, n	310
Two-sided significance level (1-alpha)	95
Power (1-beta, % chance of detecting)	80
Ratio of sample size, unexposed/exposed	1
Percent of unexposed with outcome	5
Percent of exposed with outcome	15
Odds ratio	3.4
Risk/prevalence ratio	3
Risk/Prevalence difference	10

**Table 3 table3:** Comparison of sample sizes for exposed and nonexposed groups in Kelsey and Fleiss methods.

Variables	Kelsey (n=274), n (%)	Fleiss (n=272), n (%)	Fleiss with CC^a^ (n=310), n (%)
Sample size, exposed	137 (50)	136 (50)	155 (50)
Sample size, nonexposed	137 (50)	136 (50)	155 (50)

^a^CC: continuity correction.

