#### Tools and Instruments

This study will comprise 3 evaluations: health literacy, health, and socioeconomic status. There are 8 parts to the questionnaire, which are outlined in Table 4.

**Table 4 table4:** Components of the questionnaire.

Component	Description
Part 1: Housing and the environment (head of household only)	Part 1 will capture family structure, household transportation, and water supply.
Part 2: Household income (head of household only)	Part 2 will record the household's annual income from all sources.
Part 3: Sociodemographic characteristics (all household members, including the head of household)	Part 3 will capture sociodemographic information such as date of birth, ethnicity, education, employment status, relationship status, and so on.
Part 4: Health care expenditure and utilization (all household members, including the head of household)	Part 4 questions will capture data on health payments, health care service utilization, traditional and complementary medicine practice, and health care expenditure.
Part 5: Modifiable lifestyle factors (all household members, including the head of household)	Part 5 will ask about tobacco consumption, nutrition, physical activity, and medical conditions.
Part 6: Medical information (all household members, including the head of household)	Part 6 will measure the height, weight, waist circumference, and hip circumference. The calibrated vertical SECA portable 217 stadiometer (SECA GmBH & Co KG) will be used to measure respondents’ height, the calibrated SECA 813 digital electronic weighing scale will measure weight, and the SECA 201 ergonomic measuring tape will measure waist (abdominal) and hip circumferences.
Part 7: Quality of life (all household members, including the head of household)	Questions in part 7 will assess the participant's quality of life using standard and generic methods.

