#### Data Analysis Procedure

The data analysis procedure will involve both descriptive and analytical analyses. Initially, a descriptive analysis will focus on the sociodemographic characteristics of the study population. We will examine the distribution of study variables by calculating frequency and percentage, along with reporting mean and SD. Since the outcome of interest is categorical, nonparametric tests will be used. Following the approach outlined in [26], responses categorized as inadequate and problematic will be grouped as inadequate (0), while those categorized as sufficient and excellent will be classified as adequate (1) during the analysis.

For the analytical analysis, we will carry out both bivariate and multivariate analyses to explore the determinants of health literacy among both the study population residing whining the PNP and the population living outside the PNP. This comparative approach will aim to determine which ecosystem has adequate health literacy. The significance level has been set to *P*<.05. The analytical analysis will be conducted using SPSS software (version 28.0, IBM Corp).

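### Two adults are taken from each sampled house, but neither the sample-size figures nor the named tests allow for household clustering, which matters for the prevalence and for factors shared by a house

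*Protocol article*

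**What the plan says.** All references are to the Protocol article, Methods, Phase 3.

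- **Sampling unit.** Under Participants and Sampling, every village is visited and houses are drawn within it: "The choice of houses in the village will be selected randomly based on the number of houses given by the head of the village".
- **Who is interviewed.** Under Data Collection Procedure, "The face-to-face interview will begin shortly after the head of the household and other household members have signed the consent form". A house whose head is absent at two visits is dropped as a whole.
- **Number of houses.** Under Sample Size, "we will distribute a sample size of 400 people based on the ratio calculated", and "approximately 200 households will need to be interviewed based on the assumption that 1 household has 2 adults".
- **Required size.** The same section gives 310 by the odds-ratio method (Tables 2 and 3). For the prevalence method, "the minimum sample size calculated for this study is 323 people for a 95% CI". The larger figure is adopted, raised to about 355 for 10% dropout, and then set at 400. The step to 400 is not described as an allowance for clustering.
- **Analysis.** Under Data Analysis Procedure, "Since the outcome of interest is categorical, nonparametric tests will be used". Two-variable and multivariable analyses in SPSS at a 5% significance level follow. Neither that section nor Data Entry and Analysis mentions the household.
- **Predictors recorded once per house.** In Table 4, Part 1 (housing and environment) and Part 2 are answered by the head alone: "Part 2: Household income (head of household only".

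**The concern.** Two adults under one roof share income, housing, distance to care and often schooling. Their health literacy answers are therefore likely to resemble each other, and the second adult adds less information than a fresh person from another house would. A calculation that counts 400 independent people overstates the precision of the prevalence.

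The effect is greatest for predictors that take the same value for both adults: income, housing, village, usually ethnicity, and inside versus outside the park. Several of these are what the survey is meant to study. Data Entry and Analysis names socioeconomic status as a predictor, and Data Analysis Procedure sets out the comparison of people inside and outside the park. Phase 3 results then feed the choice of intervention in phase 4 and its costing in phase 5, so a determinant wrongly declared significant would carry forward.

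**Working it through.** **Step 1: reproduce the plan's figures.**

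*Odds-ratio method.* Inputs from Tables 2 and 3 and the text: 5% in the unexposed, OR 3.41, two-sided 5%, power 80%, ratio 1:1.

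- Rate in the exposed = 3.41 × 0.05 / (0.95 + 3.41 × 0.05) = 0.1705 / 1.1205 = 0.152.
- The Fleiss two-proportion formula gives 136 per group (272 in all). With continuity correction it gives 155 per group (310 in all). Both match the protocol exactly.

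*Prevalence method.* The proportion is 35.5% at 95% confidence. The margin and the population size are not stated.

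- With an assumed 5-point margin: 1.96² × 0.355 × 0.645 / 0.05² = 352.
- With a finite population correction for an assumed 5050 adults (2525 households × 2): 352 / (1 + 351/5050) = 329, close to 323. With N = 2525 it gives 309. A population of about 3,900 would give 323.

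*Dropout.* 323 × 1.10 = 355.

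Every one of these formulas assumes independent people, and none contains a design effect.

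**Step 2: apply the design.** With m = 2 adults per house, the design effect is 1 + (m − 1) × ICC = 1 + ICC. The ICC is an assumption, shown as a range.

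- Effective size = 400 / (1 + ICC).
- True standard error / naive standard error = √(1 + ICC), for the prevalence and for factors shared by the house.
- Real type I error for a shared factor = 2 × [1 − Φ(1.96 / √(1 + ICC))].
- Half-width = 1.96 × √(0.355 × 0.645 × (1 + ICC) / 400), without finite population correction.
- Adults to recruit for an effective 323 after 10% loss = 323 × (1 + ICC) / 0.9.
- Power is for 5% versus 15% in two equal groups, 400 adults before dropout, without continuity correction.

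| ICC | Effective size of 400 | SE ratio | Type I error, shared factor | Half-width (points) | Adults for effective 323 | Power |
|---|---|---|---|---|---|---|
| 0 | 400 | 1.00 | 5.0% | 4.7 | 359 | 92% |
| 0.1 | 364 | 1.05 | 6.2% | 4.9 | 395 | 89% |
| 0.2 | 333 | 1.10 | 7.4% | 5.1 | 431 | 86% |
| 0.3 | 308 | 1.14 | 8.6% | 5.3 | 467 | 84% |
| 0.5 | 267 | 1.22 | 11.0% | 5.7 | 539 | 78% |

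A simulation of 200 houses of two with a house-level factor gave 7.6%, 8.9% and 11.2% at ICC 0.2, 0.3 and 0.5, in line with the formula.

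**Step 3: where the margin runs out.** The 400 adults are worth at least 323 while ICC ≤ 400/323 − 1 = 0.24. With 360 evaluable (10% loss), the limit is 360/323 − 1 = 0.11.

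**The case against.** - **The analysis text is silent, not wrong.** Data Analysis Procedure never says that people will be treated as independent. It names no chi-square test and no ordinary logistic model, and GEE in SPSS would also count as a multivariable analysis. A separate analysis plan could supply the household term. This stands as a limit: a reader might infer that the protocol commits to independent-data tests, and it does not. The sample-size section is different. It states independent-person figures and two adults per house side by side.
- **The required size is 323, not 400.** The extra adults absorb part of the loss, and power for the odds-ratio target stays at or above 84% up to an ICC of 0.3 before dropout. This stands. A reader might infer that the survey is too small, but the documents support that only above an ICC of about 0.24, or about 0.11 after dropout.
- **Not every determinant is affected.** Parts 3 to 7 of Table 4 are recorded per person. For factors that differ within a house, the naive standard error can be about right or even too large. This stands.
- **No margin of error is stated.** There is thus no declared precision to call wrong. With the finite population correction for an assumed 5050 adults, 360 evaluable gives about 4.8 points if independent, and 5.2 to 5.8 at ICC 0.2 to 0.5. Without the correction the figures are 4.9, and 5.4 to 6.0. A single corrected figure cannot be imposed from outside.
- **Who answers Part 8 is not spelled out.** Table 4 does not say which members complete the health literacy questions. The sizing by adults implies all of them.

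**Conclusion.** The point holds in a limited form. The house is the sampled unit, with about two adults in each. The figures of 310 (exactly) and 323 (approximately, under the stated assumptions) reproduce from independent-person formulas, and nothing in the named analysis uses the household.

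Under any positive ICC, ordinary tests would give too-narrow intervals for the prevalence. For factors common to the house, the real type I error would be about 6% to 11% for ICC 0.1 to 0.5.

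Three assumptions carry this: a positive within-house correlation, which is plausible but not given; two adults in every house; and an analysis without a household term, which is what the protocol describes but which an unseen plan could change. The prevalence estimate itself is not biased when houses contribute equal pairs. A reader might infer that all intervals and P values in the survey will be wrong; the documents do not support that. The inflation is moderate. It should be fixed, but it does not undermine the survey.

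**What to change.** **Data Analysis Procedure.** Keep a household identifier in the data file and analyse with household as the cluster. Two routes would do: logistic regression by GEE with robust standard errors, or SPSS Complex Samples with Rao-Scott tests for the two-variable step. As strata, use the three groups behind the 24%, 64% and 12% allocation, or the villages with the sparse ones merged. Unmerged villages do not work well, because Table 1 gives Jeram Aur and Sg Tabung/Teresek 2 adults each. That is about one house, which leaves no between-house variance to estimate.

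**Sample Size.** State an assumed ICC, the design effect and the resulting effective sample size of 400 adults. Give the margin of error and any finite population correction on the same basis as the 323 calculation.

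**Cost.** No extra respondents are needed for valid inference; the price is slightly wider intervals. The project manager already checks answer booklets against households surveyed (Data Security), so the identifier should be easy to record. Enrollment is under way, so this should be secured now.
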